Patient Outcomes	Clinical Deterioration Events (CDEs) [13] defined as an unplanned transfer to a higher level of care (i.e., ICU), use of an ICU intervention on the ward (vasoactive infusion, invasive or noninvasive mechanical ventilation, or cardiopulmonary resuscitation), or a ward death in a patient without limitations on resuscitation	- Prospective de-identified registry of all CDEs in hospitalized pediatric oncology patients collected by the site team - For each CDE, a de-identified case report form is completed by local site leads and entered in REDCap database by a study team member - Data analysis checks for missing and incorrect values assure data quality - Pre and post intervention measurements

^a^CritCom and the network survey will be collected concurrently during Aim 1, with CritCom collected alone during Aim 3

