In addition to impact on communication quality, we will explore intervention impact on secondary provider and patient effectiveness outcomes. *Provider outcomes* include burnout and retention and *patient outcomes*include clinical deterioration event mortality and safety/adverse events (cardiopulmonary arrest, cardiac arrest) [84]. These are considered exploratory as the trial is not powered to evaluate intervention effectiveness. We will evaluate these exploratory outcomes at three time points: baseline, three months after intervention, and six months after intervention. Provider outcomes will be based on self-report survey items collected along with the CritCom survey and demographic information. Patient outcomes will be reported by site leads via a de-identified prospective registry of all clinical deterioration events, defined as unplanned transfers to intensive care (ICU), the use of ICU interventions on general wards, or unplanned death on the ward [12]. All exploratory outcomes will be assessed as changes from baseline at 6 months.

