#### Data analysis

Data will be managed, cleaned, and analyzed in R. As a pilot, this study is not powered to formally test effectiveness, and data analysis will focus on the feasibility of the intervention and procedures in preparation for a future trial. Data will be reported using descriptive comparisons by randomization assignment. We will describe participant and hospital characteristics overall and separately by arm. Categorical variables will be reported as N (%) and continuous variables will be reported as mean ± SD or median and interquartile range, as appropriate.

The measures of feasibility, appropriateness, and acceptability are assessed on a 5-point Likert scale. Therefore, we will report descriptive statistics of these measures prior to assessing variation via Kruskal–Wallis and Mann–Whitney tests. Data will be analyzed both at the individual and organization levels, to understand how individual and organizational factors influence intervention feasibility, appropriateness, acceptability and preliminary effectiveness. Recruitment and retention across the study will also be reported via descriptive statistics to assess feasibility of the study design and procedures for a future trial.

To evaluate the preliminary effectiveness of the intervention on perceived communication quality, we will use a linear mixed model approach where intervention is included as a fixed effect (intervention or control) along with randomization assignment, baseline score, time, and the interaction between time and intervention. We will evaluate the preliminary efficacy using a linear contrast to estimate the mean difference in communication quality (CritCom scores overall and by domain) from baseline to 6 months. To account for clustering due to individual- and hospital-level repeated measurements, we will include random terms for both in our mixed model. Exploratory provider and patient outcomes will be compared between the two randomization arms using the same mixed-effect analytic approach described for the primary effectiveness outcome. We will also conduct hospital-specific subgroup analyses to explore heterogeneity in intervention effects across hospitals.

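### The linear mixed model written for CritCom scores does not suit deaths and arrests, and deterioration-event mortality rests on a denominator the intervention may change

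*Protocol article*

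**What the plan says.** In the protocol article, Aim 3, Data analysis, the CritCom model is introduced as follows: "we will use a linear mixed model approach where intervention is included as a fixed effect (intervention or control) along with randomization assignment, baseline score," with time and the time-by-intervention interaction completing the list. On clustering it adds: "To account for clustering due to individual- and hospital-level repeated measurements, we will include random terms for both in our mixed model". The patient outcomes are then assigned to it in these words: "Exploratory provider and patient outcomes will be compared between the two randomization arms using the same mixed-effect analytic approach described for the primary effectiveness outcome".

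Under Aim 3, Measures, those patient outcomes "include clinical deterioration event mortality and safety/adverse events (cardiopulmonary arrest, cardiac arrest"). The same section says: "All exploratory outcomes will be assessed as changes from baseline at 6 months". On their status it says: "These are considered exploratory as the trial is not powered to evaluate intervention effectiveness".

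The data come from a de-identified registry with one form per event, completed by the site lead or a delegate (Table 2; Aim 3, Data collection). No admissions or inpatient-days are listed among the measures or the hospital-level covariates.

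The event itself is described twice. Measures has it "defined as unplanned transfers to intensive care (ICU), the use of ICU interventions on general wards, or unplanned death on the ward". Table 2 words the last component as "or a ward death in a patient without limitations on resuscitation".

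**The concern.** Three things are at issue.

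- **Fit of model to data.** The CritCom model assumes a roughly continuous score, measured repeatedly in the same clinician, with a baseline value for each. A death is binary and happens once; an arrest is a binary event or a count. The children with events before the intervention are normally not those with events after it.
- **Denominator.** Mortality among CDEs conditions on an event that occurs after randomisation. The Background argues that communication affects how teams both recognise and manage deterioration. The intervention may therefore change how many events occur or are recorded, and with that the proportion who die, whatever happens to the number of deaths.
- **Definition.** A ward death that meets one description of a CDE and not the other enters or leaves the numerator and the denominator together.

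The pilot is meant to prepare a hybrid implementation-effectiveness trial. A mortality signal that is hard to interpret, in either direction, could carry into its planning.

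**Working it through.** The article gives no sample size, power or numerical target for these outcomes, so there is no published figure to reproduce. Two checks and one comparison of text were made.

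**1. Can the stated model be estimated on event-level data?**

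From the article: 8 hospitals, 1:1 allocation, three time points. Assumed: 20 CDEs per hospital and period, one CDE per child, about 30% mortality.

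- Rows: 8 × 3 × 20 = 480, from 480 different children. Children with both a baseline and a later row: 0. No individual baseline score exists.
- With one row per child, the variance of the outcome vector is σ²(hospital) × (block matrix) + [σ²(child) + σ²(residual)] × I. Only the sum in brackets can be estimated. The check confirmed that ZZ′ for the child term equals the identity matrix, so the child variance cannot be separated from the residual.
- Reduced versions do run. Hospital-period rates give 8 × 3 = 24 rows, or 8 × 2 = 16 post-baseline rows with each hospital's own baseline rate as covariate. A linear mixed model with a hospital term only converged on the 16 rows, and a linear probability model on the 480 rows with a hospital term only also converged; the run gave boundary warnings. Both drop the individual term, and the second also drops the baseline score, so neither is the model the article describes.

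**2. How far can CDE mortality move when deaths do not?**

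CDE mortality = deaths / CDEs. The denominator is inferred from the outcome's name and from a registry that holds only CDEs. The starting value of 30% is the mortality the Background reports from prior work in low-resource hospitals. The base of 100 CDEs and the changes in count are assumptions.

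| Change in CDE count | Deaths / CDEs | CDE mortality |
|---|---|---|
| × 0.8 | 30 / 80 | 37.5% |
| × 1.0 | 30 / 100 | 30.0% |
| × 1.2 | 30 / 120 | 25.0% |
| × 1.5 | 30 / 150 | 20.0% |

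The measure can also move against the truth. If 5 deaths and 25 survivable CDEs are prevented, deaths fall from 30 to 25 and CDEs from 100 to 100 − 5 − 25 = 70. Mortality becomes 25/70 = 35.7%, an apparent worsening although fewer children died.

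**3. The two descriptions of a CDE**

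Table 2 restricts ward deaths by resuscitation status; Measures restricts them by whether they were unplanned. The two need not select the same deaths. If 5 deaths (assumed) met only one description, 30/100 would become 35/105 = 33.3%.

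**The case against.** The strongest reply is that the article does not demand an event-level Gaussian fit. It speaks of the same approach, which could be read to include a generalised mixed model. Aim 3, Data collection, says patient outcomes are collected at hospital level, and a hospital, unlike a child, can have a change from baseline. The Missing data section allows transformations or alternative tests where needed. Part of this stands: hospital-period versions can be fitted, so a reader who infers that no version of the model could be fitted goes too far. But the approach referred to is explicitly linear with an individual term, the registry is filled in event by event, and the general clause names no alternative.

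A reader might also infer that the analysis would be improvised after the data are seen. The documents do not show this: the article is condensed, and an analysis plan may settle the distribution and the unit of analysis. The point is only that the method the article does state does not suit these outcomes.

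On the denominator, CDEs are defined by concrete acts and data checks are planned, which limits loose recording. Thresholds for transfer could still shift, and a true change in event frequency has the same effect. The size of any shift is unknown, so the table shows sensitivity and is not evidence of bias.

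On the definition, the wording in Measures may simply abbreviate Table 2. That is plausible, but the text does not say so.

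Finally, these outcomes are exploratory and unpowered, and no decision is tied to them. That stands, and it limits the severity.

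**Conclusion.** The concern holds in a limited form. As written, the CritCom model does not suit the patient outcomes: the individual baseline and individual random term have no counterpart in events among different children, and a Gaussian model is unsuitable for single binary events or rare counts. Only a reduced model, such as hospital-period rates with a hospital term, can be fitted. CDE mortality by itself is ambiguous, because the count beneath it may respond to the intervention. In the illustration it ranges from 37.5% to 20.0% with deaths unchanged. The two descriptions of ward death need reconciling.

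This rests on three assumptions: that children seldom have events in more than one period, that the denominator is recorded CDEs, and that the intervention could change how often CDEs occur or are recorded. It does not follow that a fall in CDE mortality would be spurious; the measure alone could not tell. Severity is minor to moderate.

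**What to change.** - **Analysis.** State that patient outcomes are analysed at hospital-period level with a hospital random term only, plus arm and period. Use a binomial mixed model for deaths out of CDEs, and a Poisson or negative binomial mixed model for CDEs, CDE deaths and arrests with log inpatient-days as offset. Alternatively, compare the 8 hospital-level changes by a permutation test restricted to the allocations that the balancing on baseline CritCom allows. Even unrestricted, 4 versus 4 gives only 70 allocations and a smallest two-sided p of 2/70 = 0.029; restriction makes the test coarser. Count models are also fragile with 8 clusters and rare arrests, so present the results as descriptive.
- **Reporting.** Give CDEs and CDE deaths per 1,000 oncology inpatient-days beside CDE mortality. The binomial model alone keeps the movable denominator, so the rates are needed next to it.
- **Definition.** Reconcile the CDE wording in Table 2 and in Aim 3, Measures, so that one definition applies throughout.

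The cost is a change of wording plus one extra census figure per hospital and period. It is assumed, not stated in the article, that sites can supply that figure; it is easiest to arrange before data collection starts.

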#### Missing data

We anticipate having little missing data, due to our oversight and engagement strategies and observed response rates in our prior work [88, 89]. However, we will evaluate patterns in missing data and will analytically address missing data to avoid biasing the results. We will assume that data are missing at random, and mixed-effects models produce unbiased estimates in the presence of data missing at random [90]. We will ensure that our data meets all assumptions for statistical tests and will use data transformation or appropriate test alternatives as needed.

### Dissemination plan

Our dissemination plan incorporates different audiences, including clinicians, researchers, and funders. We will share our findings through publication and conference presentations. All study team members, including members of the Expert Panel, will participate in authoring and publishing manuscripts. During the study, we will disseminate data to participating hospitals via reports, dashboards, and annual webinars [91]. Findings will also be shared with the global pediatric oncology community regularly through the St. Jude Global Alliance. All data that are produced will be made publicly available. We will focus on translational products to amplify impact and future scale, including dissemination of public goods [92] such as our measurement tools and intervention materials. Quantitative data from this study will be made available after data collection, cleaning, and de-identification. Additionally, we will make available all codebooks and results from the qualitative components.

## Discussion

The TeamTalk study aims to develop a rigorous understanding of modifiable aspects of communication quality and structure to inform a co-developed, contextually responsive, feasible, and effective intervention to improve team communication and care for children with cancer across resource-variable hospitals globally. This study will provide a foundational understanding of modifiable determinants of team communication that impact pediatric cancer care to inform a multilevel intervention that responds to these determinants to improve childhood cancer outcomes. Ultimately, this work will improve team communication and outcomes for children with cancer in hospitals of all resource levels, thus advancing health equity globally.

This study is innovative in several ways. We will leverage implementation science and social network methods to focus on the relationship between communication structure and quality, and how they impact health outcomes, an important conceptual innovation. Additionally, this study will advance pragmatic multi-lingual measurement for team communication by using CritCom, a novel, reliable, multilingual measure of team communication. This measure was designed for clinical healthcare team use globally. This work will continue to provide construct validity for this pragmatic measure, advancing communication measurement in different linguistic settings, which is a major scientific barrier within the field. This work will shift approaches in how communication quality can be measured in clinical settings, resulting in opportunities to assess communication more broadly. Finally, this study emphasizes that improving team teamwork is a priority within cancer care [93–95], and quality of communication within teams impacts patient and provider outcomes [25, 26, 96–99]. To our knowledge, this will be the first study in pediatric oncology connecting provider- and hospital-level determinants to team communication structure and quality. Taken with prior work linking communication to outcomes, this research will provide novel empirical evidence to inform rigorous development of interventions to improve communication.

This study integrates implementation science theory to expedite the implementation of an evidence-informed, co-designed novel communication intervention in resource-variable settings. Many barriers limit implementation of new healthcare innovations [100]. On average, it takes 17 years for evidence to progress from discovery to delivery [101], and this timeframe is likely longer in low-resource settings. However, some models promote the continual improvement of care processes, which would ultimately increase high-quality healthcare. This proposal uses rapid, streamlined, participatory methods to identify local strengths along with relevant challenges to care delivery, then quickly leverage this contextual knowledge to develop and implement interventions to address identified challenges. This work thus provides important knowledge about how to effectively intervene on communication barriers by identifying communication facilitators and building on existing communicating supports to improve care. We have informed this study with implementation science principles to promote accelerated knowledge translation [102, 103] thus enhancing dissemination and the future scalability of these efforts. We expect the results of this work to advance health services research by establishing a rigorous approach for developing theoretically driven, empirically informed novel interventions that result in advances in care delivery in a range of clinical settings across all resource-levels.

Prior work demonstrates that effective team communication is a crucial determinant of quality care for children with cancer [93, 104, 105], yet little is known about how clinician communication networks vary across hospitals with different resource-levels and how these variations relate to care delivery. This study directly addresses this knowledge gap. This work will broaden our understanding of the role of healthcare team communication in pediatric cancer care through advancing the use of a novel measure of team communication quality and the development of an appropriate and feasible intervention. Ultimately, this research will design an intervention to make high-quality communication more likely, therefore having a direct impact on clinical practice and improve childhood cancer outcomes. This study will also allow for future work to evaluate both the implementation and effectiveness of this novel intervention in a larger hybrid-effectiveness trial, with a focus towards global scale-up and sustainability.

## Data Availability

Not applicable.

## Abbreviations

CDE: Clinical Deterioration Event
CritCom: A measure of team communication during pediatric deterioration
cMTS: Cancer Multiteam System framework
ICU: Intensive Care Unit
TeamTalk: The name given to this project to study team communication during healthcare delivery
WHO: World Health Organization
